## Abstract

**Background:**

Asthma is a major health problem and has significant mortality around the world. Although the symptoms can be controlled by drug treatment in most patients, effective low-risk, non-drug strategies could constitute a significant advance in asthma management. An increasing number of patients with asthma are attracted by acupuncture and moxibustion. Therefore, it is of importance that scientific evidence about the efficacy of this type of therapy is regarded. Our past researches suggested heat-sensitive moxibustion might be effective in treatment of asthma. Our objective is to investigate the effectiveness of heat-sensitive moxibustion compared with conventional drug treatment.

**Methods/Design:**

This study is comprised of a multi-centre (12 centers in China), randomized, controlled trial with two parallel arms (A: heat-sensitive moxibustion; B: conventional drug). Group A selects heat- sensitive acupoints from the rectangle region which consist of two outer lateral lines of dorsal Bladder Meridian of Foot-Taiyang, and two horizontal lines of BL13(Fei Shu) and BL17 (Ge Shu);6 inch outer the first and second rib gap of anterior chest. Group B treats with fluticasone/salmeterol (seretide). The outcome measures will be assessed over a 3-month period before each clinic visit at days 15, 30, 60, and 90. Follow-up visit will be at 3, 6 months after the last treatment session. Adverse event information will be collected at each clinic visit.

**Discussion:**

This trial will utilize high quality trial methodologies in accordance with CONSORT guidelines. It may provide evidence for the effectiveness of heat-sensitive moxibustion as a treatment for chronic moderate persistent asthma. Moreover, the result may propose a new type moxibustion to control asthma.

**Trial Registration:**

The trial is registered at Chinese Clinical Trials Registry: ChiCTR-TRC-09000599

## Background

Asthma is a common chronic inflammatory disease of the airways characterized by variable and recurring symptoms, airflow obstruction, and bronchospasm [1]. It is also a complex disease involving many cells and mediators[2]. Asthma affects 300 million people worldwide[3], with an increasing prevalence in Western Europe(5%) and the USA(7%) in particular[4,5]. Despite the fact that there is still no cure for asthma, it has been established in a great number of small and large studies that many patients can reach a good asthma control with controller treatment [6]. Generally speaking, Medications used to treat asthma are divided into two general classes: quick-relief medications used to treat acute symptoms and long-term control medications used to prevent further exacerbation [7]. The therapeutic options available for patients with asthma depend on the severity of the condition. Although the symptoms can be controlled by drug treatment in most patients, effective low-risk, non-drug strategies could constitute a significant advance in asthma management [1-3]. Therefore, an increasing number of patients with asthma are attracted by complementary and alternative medicine (CAM) [8]. A survey showed that roughly 50% of asthma patients used some form of unconventional therapy [9].

Acupuncture has traditionally been used in asthma treatment in China and is increasingly applied for this purpose in Western countries. Moxibustion is a traditional Chinese method of acupuncture treatment, which utilizes the heat generated by burning Moxa (it is also called Mugwort or Moxa) to stimulate the acupuncture points. The technique consists of lighting a moxa-stick and bringing it close to the skin until it produces hyperemia due to local vasodilatation. The intensity of moxibustion is just below the individual tolerability threshold. Moxibustion has anti-inflammatory or immunomodulatory effects against chronic inflammatory conditions in humans [10]. Moxibustion method for treatment of asthma diverse curative effect and its mechanism may be due to improve lung function, antagonize of inflammatory mediators, modulate of immune function, regulate the role of cyclic nucleotide levels, and can also affect the neuroendocrine network and inflammatory cells[11-14]. Therefore, these inflammatory substances may be reduced and weakened by moxibustion. Especially for chronic persistent asthma, moxibustion may get a better effect.

Although firm evidence has not been established, the results of some clinical trials suggest that acupuncture and moxibustion may effective in the treatment of asthma [15-18]. However, these researches do not confirm the efficacy of acupuncture and moxibustion. This may be because all relevant RCTs were limited by methodological defects, including inappropriate sample size, variability of acupuncture and sham protocols, and missing information. Therefore, rigorous high-quality randomized controlled trials are needed.

Thinking about moxibustion itself, the selection of location for manipulating Moxa plays an important role in obtaining good effects [19]. The moxibustion point location may be connected with the changes in the condition of the disease. Our team of experts were astonished to find that the main factor in selecting the location of acupuncture points is link with the area which is affected by disease, not only the standardized fixed position.

In the human nature, there are two state of being in acupuncture points, the sensitized or awake state and the rest state. When the human body suffers form disease, the acupoints on the surface of the body are stimulated and sensitive by various stimulants including heat. The specific areas stimulated by heat are then called "heat-sensitive points". One of the characteristics of these areas is that they are specific or closely related to acupuncture points and have the same clinical effect as "a small stimulation induces a large response". The *Inner Canon of Huangdi *or *Yellow Emperor's Inner Canon *is an ancient Chinese medical text that has been treated as the fundamental doctrinal source for Chinese medicine for more than two millennia and until today. According with its core viewpoint and theory, acupoint is described and understood with the state, which is certain area of the body surface in the course of diseases. Among the changes, sensitized status is the common one, described that acupoints on the body surface may be sensitized in the course of diseases. Acupoint heat-sensitization is a type of acupoint sensitization. Our research found that the heat-sensitive phenomenon to a point or an area is a new type of reaction featured in a pathological state [20-23]. We applicated the acupoint heat-sensitization phenomenon and rule in the past twenty years. Our team experimental evidence indicates that the state of a point might change from the rest state to the heat sensitized state while suffering from diseases. Its characteristic was thought that these special acupoints might produce heat response and farther warm sensation, as a result of stimulation of moxibustion heat. If we can search out these heat-sensitized acupoints associating with pathological state, good effect will be achieved. Therefore, selecting the heat-sensitized acupoint may obtain therapeutic effect far better than acupuncture and moxibustion at acupoints of routine rest state. So we defined the approach which treated various diseases through heat-sensitized acupoint, as heat- sensitive moxibustion therapy. We carried out many clinical trials to test and verify the efficacy of heat-sensitized acupoint, such as myofascial pain syndrome [22], lumbar disc herniation [24], pressure sores [25] and knee osteoarthritis [26]. The result of clinical trials almost suggested superiority effect of heat-sensitized acupoint and encouraged us to proceed. Hence, we planned a rigorous multi-centre randomized controlled trial with a large sample size.

## Method/design

### Objective

The aim of this study is to investigate the effectiveness of heat-sensitive moxibustion compared with fluticasone/salmeterol (seretide) in patients with chronic moderate persistent asthma in China.

### Outcome measures

#### Primary outcome

At present, the goal of asthma care is to achieve and maintain control of clinical manifestation of the disease [27,28]. Hence, we use Asthma Control Test (ACT) to quickly access asthma control, a simple 5-question tool that is completed by the patient and parents/caregivers and recognized by the National Institutes of Health (Table 1)[29,30]. Patients should write the number of each answer in the score box provided, and then add up each score box for your total. ACT will be assessed before treatment and at days 15, 30, 60, and 90 in the treatment period. Follow-up visit will be at 3, 6 months after the last treatment session.

**Table 1 T1:** Asthma Control Test (ACT) for people 12 yrs and older.

1. In the past 4 weeks, how much of the time did your asthma keep you from getting as much done at work, school or at home?					Score
All of the time ①	Most of the time ②	Some of the time ③	A little of the time ④	None of the time ⑤	

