**2. During the past 4 weeks, how often have you had shortness of breath?**					

More than once a day ①	Once a day ②	3 to 6 times a week ③	Once or twice a week ④	Not at all ⑤	

**3. During the past 4 weeks, how often did your asthma symptoms (wheezing, coughing, shortness of breath, chest tightness or pain) wake you up at night or earlier than usual in the morning?**					

4 or more nights a week ①	2 or 3 nights a week ②	Once a week ③	Once or twice ④	Not at all ⑤	

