**5. How would you rate your asthma control during the past 4 weeks?**					

Not controlled at all ①	Poorly controlled ②	Somewhat controlled ③	Well controlled ④	Completely controlled ⑤	

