### Design

A multi-centre, randomized, two parallel arms (group A and B) and assessor blinded, positive controlled trial will be conducted at the twelve centers in China (Table 2).

**Table 2 T2:** List of 12 clinical centers

Name	City	Province
Affiliated Hospital of Jiangxi University of Traditional Chinese Medicine(TCM)	Nanchang	Jiangxi

Guangdong Hospital of Traditional Chinese and Western Medicine	Foshan	Guangdong

Wuhan the First Hospital	Wuhan	Hubei

Guangdong Hospital of TCM	Guangzhou	Guangdong

Guangzhou University of TCM	Guangzhou	Guangdong

Guangdong Disabled Soldier Hospital	Guangzhou	Guangdong

Affiliated Hospital of Shandong University of TCM	Jinan	Shandong

Suzhou Hospital of TCM	Suzhou	Jiangsu

The First Affiliated Hospital of Zhejiang University of TCM	Hangzhou	Zhejiang

The First Affiliated Hospital of Chongqing Medical University	Chongqing	Chongqing

The First Affiliated Hospital of Nanchang University	Nanchang	Jiangxi

Nanchang Hospital of Traditional Chinese and Western Medicine	Nanchang	Jiangxi

The study will be sequentially conducted as follows: a run-in period of one week prior to randomization, a treatment period of 90 days, and a follow-up period of six months. At the end of the run-in period, participants will be randomized to the heat-sensitive moxibustion group or the drug group by the central randomization system (Figure 1). This system is provided by China Academy of Chinese Medical Sciences, which adopted the computer telephone integration (CTI) technology to integrate computer, internet and telecom. The random number list will be assigned by interactive voice response (IVR) and interactive web response (IWR) [31]. The success of blinding will be assessed at each participant's last visit. Assessor who did not participate in the treatment and who is blinded to the allocation results will perform the outcome assessment.

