#### Outcome data

For primary and secondary outcome measures, these will be summarized descriptively (mean, SD, median, minimum and maximum) at each time point by treatment group. The t-test, Mann-Whitney U and Wilcoxon test were used for comparison of variables, as appropriate.

All adverse events reported during the study will be included in the case report forms; the incidence of adverse events will be calculated. The percentage of subjects with adverse events in each group will be calculated and compared using the chi-squared test or Fisher's exact test.

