##### Dropped or missing data

Reasons for dropped or missing data will be explored by descriptively. Missing data will be replaced according to the principle of the last observation carried forward.

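### ACT recalls 4 weeks, so 46% of the period scored at day 15 precedes treatment: any between-group ACT test at that visit is attenuated, while the day-90 comparison is touched only slightly, through LOCF

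*Protocol article*

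**What the plan says.** Everything here is in the Protocol article.

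- **Schedule** (Outcome measures, Primary outcome): "ACT will be assessed before treatment and at days 15, 30, 60, and 90 in the treatment period".
- **Recall period** (Table 1): all five items use the same 4-week window. Item 2 reads "During the past 4 weeks, how often have you had shortness of breath" and the global item reads "How would you rate your asthma control during the past 4 weeks". No shorter recall is given for day 15.
- **Timeline** (Design): "a run-in period of one week prior to randomization, a treatment period of 90 days".
- **Analysis** (Outcome data): primary and secondary outcomes are "summarized descriptively (mean, SD, median, minimum and maximum) at each time point by treatment group". The next sentence is "The t-test, Mann-Whitney U and Wilcoxon test were used for comparison of variables, as appropriate", with no visit named or excluded.
- **Missing data** (Dropped or missing data): "Missing data will be replaced according to the principle of the last observation carried forward". No limit is set on which observation may be carried.
- **Named comparisons** (Follow-up data): the primary ACT comparison is at 3 months, and the secondary ones are at 6 and 9 months.
- **Analysis set** (Statistical analysis plan): all randomised participants with at least one measurable outcome report.

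**The concern.** The recall window is longer than the time on treatment at the first post-baseline visit. The day-15 score blends on-treatment control with control during the run-in and the days before it, and it shares those earlier days with the baseline score. Randomisation makes pre-treatment control equal between the arms in expectation, so including those days pulls a between-arm difference towards zero.

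Two things are at stake. The first is how a day-15 comparison is read: a small difference could be taken as little early separation when part of it comes from the recall window. The second is indirect. A patient who leaves between days 15 and 30 has day 15 as the last ACT, and unrestricted LOCF places that partly pre-treatment score in the 3-month primary analysis. The sample size section frames the trial as non-inferiority, so anything that moves the arms together deserves a check.

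**Working it through.** The plan gives no figure for the recall overlap, so there is none to reproduce.

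**Inputs.** Recall window 4 weeks = 28 days (Table 1). ACT visits at days 15, 30, 60 and 90 (Primary outcome). Run-in 7 days (Design). Pilot difference 0.45 and margin 0.15 (Sample size). Anticipated loss to follow-up 20% (Follow-up data). Assumed: treatment starts at randomisation and day 15 counts as a treated day.

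**Step 1: share of the window before treatment** = max(0, 28 − visit day) / 28.

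| Visit | Pre-treatment days | Share |
|---|---|---|
| Day 15 | 13 (7 run-in + 6 earlier) | 13/28 = 46.4% |
| Day 30 | 0 | 0% |
| Day 60 | 0 | 0% |
| Day 90 | 0 | 0% |

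If day 15 is not counted as treated, the first share is 14/28 = 50%. Day 15 is the only on-treatment visit with an overlap.

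**Step 2: attenuation at day 15.** Assume each recalled day has equal weight, the arms are equal before treatment, and the difference D is constant on treatment. The expected day-15 difference is then D × 15/28 = 0.536 D. A difference of 1.0 point shows as 0.54, and 0.45 shows as 0.45 × 0.536 = 0.24.

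The weighting is an assumption. If, for illustration, a pre-treatment day counts half as much as a treated day, the pre-treatment share is 6.5/(6.5 + 15) = 30% and the difference shows at 0.70 D. Heavier weight on recent days reduces the attenuation but does not change its direction.

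**Step 3: effect on day 90 through LOCF.** Let x be the share of patients, equal in both arms, whose day-15 score is carried to day 90. The expected difference is (1 − x)D + x(0.536 D) = D(1 − 0.464x).

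| x (assumed) | Factor | Shrinkage | On a difference of 0.45 |
|---|---|---|---|
| 5% | 0.977 | 2.3% | 0.45 × 0.023 = 0.01 |
| 10% | 0.954 | 4.6% | 0.45 × 0.046 = 0.02 |
| 20% | 0.907 | 9.3% | 0.45 × 0.093 = 0.04 |

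The plan does not state x. The 20% row is an extreme case: it puts all the loss anticipated for the whole trial between days 15 and 30.

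**Step 4: barring day 15 while LOCF stays.** The last observation for these patients would be baseline, which is wholly pre-treatment, so the factor becomes 1 − x. At x = 5% the shrinkage rises from 2.3% to 5%; at x = 20% it rises from 9.3% to 20%.

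**The case against.** The strongest reply is that no between-group test at day 15 is actually stated. The named ACT comparisons are at 3, 6 and 9 months. For each time point the plan promises only descriptive summaries, and the sentence listing the tests names no visit. Recording an interim score at day 15 is not an error in itself. This stands: the test is permitted by the wording, not specified.

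The second reply is that the primary endpoint's own window is clean. This also stands. Day 90 contains no pre-treatment days, and the only route in is LOCF for patients who leave in one fortnight.

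Three stronger readings are tempting, and the documents support none of them.

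- *Day-15 ACT cannot measure a treatment effect.* Under equal weighting 54% of the difference remains. That is attenuation, not absence.
- *The dilution favours non-inferiority.* Shrinkage towards zero does so only if moxibustion is truly worse. If it is better, shrinkage works against it. The sample size section gives no direction for the pilot difference of 0.45.
- *The cure is to forbid carrying day 15 forward.* LOCF is the only missing-data method stated, so this alone would substitute baseline and increase the dilution (step 4). Such patients might also fall out of the analysis set.

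What remains is that the article itself fixes the instrument, the visit days and an LOCF rule without limits, and that nothing in it keeps day 15 out of the between-group tests.

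**Conclusion.** The point holds as a minor one. Of the 28 days covered by the day-15 ACT, 13 (46%) precede treatment, and any between-group test there is attenuated towards no difference. The factor is about 0.54 under equal weight per recalled day and closer to 1 if recent days weigh more. The first visit free of this is day 30.

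The primary day-90 comparison is affected only through day-15 scores carried forward, and the effect is small: about 2% at an assumed 5% of patients and about 9% at 20%. On the pilot difference these are 0.01 and 0.04 points, against a margin of 0.15.

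The figures rest on equal pre-treatment control in expectation, a constant on-treatment difference, and the same early-leaver share in both arms. If early leaving differs by arm, the carried scores no longer act as simple shrinkage, and the documents do not settle which arm would lose. A reader should not infer that the primary result is materially biased or that the bias leans towards non-inferiority.

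**What to change.** 1. In Outcome data, state that day-15 ACT is reported descriptively only, as an interim score that partly reflects the pre-treatment period, and that between-group ACT comparisons start at day 30.
2. Do not simply bar the day-15 value while LOCF remains. Replace LOCF for missing day-90 ACT with a likelihood-based repeated-measures model that has a separate treatment effect at each visit, or with multiple imputation. Day 15 can then inform the missing values as an auxiliary measurement without standing in for day 90.

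**Cost.** The first change is a line of wording and gives up a formal day-15 comparison. The second needs slightly more analysis work. Patients who leave between days 15 and 30 would then contribute to day 90 through the model's missing-at-random assumption. Neither change alters a visit, the questionnaire or the sample size.

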#### Secondary outcomes

Measurement of lung function provides an assessment of the severity, reversibility, and variability of airflow limitation. Forced expiratory volume in 1 s (FEV1) and peak expiratory flow (PEV) will be used in this trial. Attack frequency also will be assessed. These outcomes also will be assessed before treatment and at days 90 in the treatment period. Follow-up visit will be at 3, 6 months after the last treatment session. Adverse event information will be collected at each clinic visit.

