### Treatment protocol

#### Heat-sensitive moxibustion

Moxibustion will be performed by certified acupuncture medical doctors at 12 centers. Qualified specialists of acupuncture in traditional Chinese medicine with at least five years of clinical experience will perform the acupuncture in this study. All treatment regimens will be standardized between 12 centers practitioners via video, hands-on training and internet workshops. Participants will be randomly assigned to the heat-sensitive moxibustion group, or the drug group. In the former group, a 22 mm (diameter) × 160 mm (length) moxa-sticks (Jiangxi Hospital of Traditional Chinese Medicine, China) will be used. The patient is usually in the comfortable position for treatment, with 24°C~30°C temperature in the room. He should wear loose clothes.

For the heat-sensitive moxibustion group, the moxa-sticks are lit by the therapist and held over the rectangle area which consist of two outer lateral lines of dorsal Bladder Meridian of Foot-Taiyang, and two horizontal lines of BL13(Fei Shu) and BL17 (Ge Shu);6 inch outer the first and second rib gap of anterior chest. The warming suspended moxibustion about distance of 3 cm above the skin are used to search the acupoint heat-sensitization phenomenon. The following patients sensation will suggest the special heat-sensitization acupoint: diathermanous sensation due to moxa-heat, defining as the heat sensation conducting from the Moxa local skin surface into deep tissue, or even into the thoracic cavity; expand heat sensation due to moxa-heat, defining as the heat sensation spreading the surrounding little by little around the moxa point; transfer heat sensation due to moxa-heat, defining as the heat sensation transferring along some pathway, or even to the arms. The therapists mark the point as heat-sensitive acupoint. We try our best to seek all the special acupoints in each patient by the repeated manipulation.

The therapists begin to treat patients from the most heat-sensitive intensity acupoint. Treatment sessions end when patients are feel the acupoint heat-sensitization phenomenon disappeared. Generally speaking, we find the time range from 30~60 minutes. In 1^st ^month, patients receive the treatment once a day in the first eight days, and 12 times treatment in the next twenty-two days. Treatments will be given 15 times a month for the remaining two months.

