##### Follow-up data

The primary outcome will be the ACT scores. The primary analysis will compare the two groups in 3 months. A secondary analysis will compare the two groups at 6,9 months to assess if any differences between groups have been maintained over time.

Loss to follow-up is likely to lead to biased estimates of intervention effect. We will try to avoid bias due to attrition by carefully following up the participants in both groups. We will phone participants who fail to complete questionnaires after a second reminder. We anticipate a 20% loss to follow-up in this trial, and will implement procedures to minimize loss to follow-up and patient withdrawal, and where possible, we will collect information on reasons for patient withdrawal.

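### Follow-up visits are counted from each patient's final treatment session but analysed as months 6 and 9, so patients who stop early and still attend are measured too soon

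*Protocol article*

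**What the plan says.** All references are to the Protocol article.

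- **Visit rule.** Primary outcome: "Follow-up visit will be at 3, 6 months after the last treatment session". The same rule stands under Secondary outcomes, for FEV1, peak flow and attack frequency, and in the Methods/Design part of the Abstract.
- **Analysis times.** Follow-up data: "A secondary analysis will compare the two groups at 6,9 months to assess if any differences between groups have been maintained over time".
- **Planned course.** Design: "a treatment period of 90 days, and a follow-up period of six months". This applies to both arms.
- **Visits during treatment.** Primary outcome: "ACT will be assessed before treatment and at days 15, 30, 60, and 90 in the treatment period". These are set by calendar day.
- **Primary analysis.** Follow-up data: "The primary analysis will compare the two groups in 3 months".
- **Who is analysed.** The Statistical analysis plan section uses intention to treat and keeps everyone randomised who supplies one or more outcome values. A patient who stops treatment early therefore stays in.

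The article does not say whether the final session means the scheduled one or the one the patient actually attended.

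**The concern.** The visit rule and the analysis run on different clocks. The visits are counted from an event that each patient can bring forward, while the comparison is labelled by time since the start. For someone who stops early, the value entered as month 6 or month 9 belongs to an earlier point.

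Stopping happens after randomisation and may be related to both arm and outcome. One arm attends repeated therapist-delivered sessions and the other uses an inhaler at home, so the rate and timing of stopping could differ. If they do, the two groups would be compared at different average times since randomisation. The stated purpose of this comparison is to see whether a difference lasts, and that question needs a common clock.

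**Working it through.** **Inputs**

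- Treatment period: 90 days, both arms (Design).
- Follow-up visits: 3 and 6 months after the final session (Primary outcome, Secondary outcomes, Abstract).
- Analysis times: 6 and 9 months (Follow-up data).
- Moxibustion: 8 + 12 = 20 sessions in month 1, then 15 in each of months 2 and 3, so 20 + 15 + 15 = 50 (Heat-sensitive moxibustion).
- Drug: 180 sessions in 90 days, which is 2 a day (Drug group).
- ACT recall: the past 4 weeks (Table 1).
- Assumptions made here: a month is 30 days, and treatment starts at randomisation.

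**Step 1. Reproduce the plan's own times.** With the final session on day 90, the visits fall on 90 + 90 = day 180 (month 6) and 90 + 180 = day 270 (month 9). The article's figures agree for a patient who completes the course.

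**Step 2. Apply the rule literally to a final session on day s.** The visits fall on days s + 90 and s + 180. Both are early by 180 - (s + 90) = 270 - (s + 180) = 90 - s days.

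| Final session (day) | First follow-up (day) | Second follow-up (day) | Days early |
|---|---|---|---|
| 15 | 105 | 195 | 75 |
| 30 | 120 | 210 | 60 |
| 60 | 150 | 240 | 30 |
| 88 | 178 | 268 | 2 |
| 90 | 180 | 270 | 0 |

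**Step 3. What this does to the ACT value.** For a patient who stops on day 15, the first follow-up score covers about days 105 - 28 = 77 to 105. The day-90 score covers about days 90 - 28 = 62 to 90. The two recall periods overlap from about day 77 to day 90, so the value used for month 6 partly repeats month 3. The second visit, on day 195, is the last one planned, and nothing is measured near day 270.

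**Step 4. Would the analysis notice?** No. A score taken early is an observed score. The rule for missing data (last observation carried forward) is not triggered, and the value enters the comparison under the nominal month.

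**Step 5. Can an average effect be computed?** No. It needs the number of patients in each arm who stop early and still attend, and when they stop. The article gives neither. Its 20% is anticipated loss to follow-up, which is a different quantity: a patient who is lost has no mistimed visit.

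**The case against.** The strongest reply is that the timetable is consistent as planned. Both arms have a 90-day course followed by six months of follow-up, so a reader could take the final session to mean the scheduled end of treatment. That stands for completers, and it may be what the authors intended. The words do not say so, however, and a site that books from the session actually attended would be following them.

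A second reply is that time since the end of treatment is a legitimate scale for asking whether an effect lasts. It is, but the analysis is labelled by months 6 and 9. A comparison of randomised groups is cleaner on a clock that treatment behaviour cannot move.

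A third is that visit windows and the handling of early stoppers belong in the full protocol, which is not shown. That is fair for those details, and their absence is not the point here. The point is a rule that the article states three times and that misfires for early stoppers.

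It is also true that the primary analysis is unaffected, because its visit is fixed at day 90. The 6- and 9-month comparison is described directly after ACT is named. The article does not say whether it extends to lung function and attack frequency, although those are measured at the same visits.

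A reader might go further and infer that the whole moxibustion arm is seen early, because the month-3 schedule fixes no spacing: "Treatments will be given 15 times a month for the remaining two months". The documents do not support that. A material shift among completers would need the month-3 sessions to be bunched at its start, which is nowhere stated. Spread over the month, they end within about 0 to 2 days of day 90. A reader might also use the 20% as a rate of stopping and derive an average shift by arm. The article gives no stopping rate and no difference between arms, so such a figure would be invented.

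**Conclusion.** The point holds in a limited form. As worded, the visit rule matches the 6- and 9-month analysis only for patients whose final session is at about day 90. A patient who stops earlier and still attends is measured 90 - s days early, for example 75 days early after stopping on day 15 and 30 days early after stopping on day 60, and is analysed as if on time.

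This rests on reading the final session as the one actually attended. It concerns the secondary follow-up comparisons only. The shift for an individual patient is exact apart from the 30-day month and the assumed start of treatment at randomisation. The effect on the group comparison is unknown in size and direction. This is a modest flaw, but it should be settled before follow-up begins, because a visit held at the wrong time cannot be repeated.

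**What to change.** In the Abstract (Methods/Design), Primary outcome and Secondary outcomes, replace the anchor with fixed times from randomisation: 6 and 9 months, that is days 180 and 270. State that this applies to every randomised patient in both arms, regardless of when treatment stopped. Record the date of the last session or dose as a separate variable.

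The follow-up visits would then use the same kind of clock as the visits on days 15, 30, 60 and 90, and would match the times already named under Follow-up data. The cost is wording in three places and a change to the visit scheduler, with no extra visits. The small downside is that time since last treatment will vary more among early stoppers. The recorded stop date allows this to be described.
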